### Other measures

Table 2 shows an overview of the other measures. Decision aid users are asked to evaluate the DA by indicating for 25 statements if it applies to the responder or not. The first 11 statements are formulated negatively (for example, ‘I found the decision aid too difficult’), followed by 14 positively formulated statements (for example, ‘I found the decision aid pleasant to use’). Although literature reports positive effects from the usage of DAs in general [47], there may be subgroups that will not benefit from DA-usage. To identify these subgroups, additional measures on (health) skills and personality are included. Objective measures for health literacy and health numeracy are used, with the HRS Experimental numeracy module [48] and the STOHFLA-brief [49], respectively. The Decision Self-Efficacy Scale is used as a subjective measure of the perceived ability to make a decision [50].

**Table 2 Tab2:** Other measures

Measures	Instrument	T1	T2	T3
Implementation (intervention only)				
DA-Acceptability	Self-developed	X		
(health) skills				
Self-efficacy	Decision self-efficacy scale	X		
Health numeracy	HRS Experimental numeracy module		X	
Health literacy	STOHFLA-brief		X	
Psychosocial variables				
Anxiety and depression	HADS, PC-max	X	X	X
Personality	LOT-R, BFI-10	X		
Information seeking preferences	API, NFC-short, Maximization scale	X		
Sociodemographics and other healthcare utilization		X	X	X

Comparable to health skills, the relation of personality to beneficial DA-usage will be investigated. Some studies suggest a link between personality and treatment choice [51, 52]. Following these studies, some relevant aspects of personality will be taken into account: hospital anxiety and depression (HADS-scale) [53], prostate specific anxiety (MAX-PC) [54, 55], optimism (Life Orientation Test - Revised) [56], the big five personality dimensions (Big Five Inventory-10) [57], information seeking preferences (subscale from the Autonomy preference index) [58] and maximization tendencies (Maximization scale) [59].

### Sociodemographic variables and additional healthcare utilization

Standard sociodemographics will be asked on age, marital status, occupation, and education. Also, patients will be asked to report any additional healthcare utilization (general practitioner or other medical specialist) in the past 12 months to assess whether this affects the decision-making process.

### Healthcare providers’ evaluation

Healthcare providers in the intervention arm will be asked their opinion about implementation of the DA in qualitative interviews as well as questionnaires at the end of patient inclusion (approximately after 12 months). This questionnaire will be based on the MIDI-instrument [60], which is developed for the evaluation of implementing an innovation in a healthcare setting. The questionnaire will focus on usage of the DA (for example, *‘Did you offer the DA to all eligible patients?’*) and evaluate the pros and cons of the DA with help of statements (for example, ‘*The DA is practical in use’*). Healthcare providers in the control condition will be asked to evaluate the current information provision and decision-making processes, their expectation of DA-usage and motivation for implementation.

### Sample size calculation

The sample size for this study is determined by power analysis with decisional conflict as the primary measure. To be able to detect a clinically relevant minimum effect size [61] of .50, power is set at .80 and alpha at .05. With 19 hospitals (clusters) that agreed to participate, it is needed to estimate the intra-class coefficient (ICC). The ICC assesses the proportion of variance explained by clusters. Higher ICC values decrease effective sample size and statistical power. ICC ranges from 0 to .1 are considered common in medical literature [62]. A more specific review of ICC values in (cluster) RCTs with psychosocial measures is provided by Bell and McKenzie [63], which also included a cluster RCT evaluating a group support tool for prostate cancer patients [64]. The median estimated value for 82 longitudinal ICCs from 15 included studies was 0.0007, and the range found for decisional conflict was between 0 and 0.02. Given the considerable variability in ICCs that is found in literature, ICC for the current trial is set conservative at 0.01.

The attrition rate is set at 25 % to compensate for non-response to the questionnaires. This rate is comparable to studies in similar populations and following the same methods as this study does [65, 66]. Calculations show that a design with 19 clusters of 20 patients (380 patients in total) achieves a power of .8. Taking into account a 25 % attrition rate between the first and third questionnaire, the total sample size (rounded) will be set at 475 patients. This results in a recruitment of 25 patients per hospital.

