### Statistical analysis

All analyses will be conducted using SPSS version 19.0 (Statistical Package for Social Sciences, Chicago, IL, USA). A 0.05-significance level will be adopted in all statistical tests.

We will perform a descriptive statistical analysis of organizational (hospitals) and socio-demographic (patients) characteristics in order to assure the comparability of the intervention and control groups. Baseline measures and changes in outcome variables over the study period for each study arm will be presented as means (± SD).

The main outcome decisional conflict is measured at T1 and will be compared between both groups (intervention and control). Multilevel modelling will be carried to take the hierarchical structure of the data into account by specifying random effects at both hospital and patient level. The least square mean proportions will be estimated and compared to assess the effect of the DA on decisional conflict.

The secondary outcomes will also be compared between both groups using multilevel modelling. Some of the secondary measures consist of repeated measures (for example, HRQoL and decisional regret) and will be treated according the appropriate mixed-model approach; that is, repeated measures anova/ancova will be used for outcomes with two time points (decisional regret, treatment satisfaction), and a random coefficient approach will be used for outcomes with three time points (HRQoL) [67]. Observed variation in treatment choice during the trial period will be compared between groups and at level of the individual hospital. For this second comparison, each hospital’s particular historical treatment variation profile (2008 to 2012) will be obtained from the Netherlands Cancer Registry.

Potentially confounding variables (for example, personality, health skills, and age) will be explored for their impact on the primary and secondary outcomes. Missing data and drop-outs will be described.

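### The stated power of .80 does not follow from the stated inputs: 19 clusters of 20, effect size .50 and ICC 0.01 give about 99%

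*Protocol article*

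**What the plan says.** All the relevant statements are in the Sample size calculation section of the protocol article.

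- Basis: "The sample size for this study is determined by power analysis with decisional conflict as the primary measure".
- Target: "To be able to detect a clinically relevant minimum effect size [61] of .50, power is set at .80 and alpha at .05".
- Clusters: "With 19 hospitals (clusters) that agreed to participate".
- ICC: "ICC for the current trial is set conservative at 0.01". The section supports this with a general range of 0 to .1, a median of 0.0007 over 82 longitudinal ICCs and, for the primary measure, "the range found for decisional conflict was between 0 and 0.02".
- Result: "Calculations show that a design with 19 clusters of 20 patients (380 patients in total) achieves a power of .8". The recruitment target of 475 (25 per hospital) is then built on these 380 patients.

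The Statistical analysis section adds only that "A 0.05-significance level will be adopted in all statistical tests". Neither section says whether the test is one-sided or two-sided.

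**The concern.** Every input needed for a standard cluster-trial power calculation is printed, so the result can be checked directly. An effect of half a standard deviation is large for 380 patients, and an ICC of 0.01 with 20 patients per cluster costs little. A power of only .80 therefore looks too low.

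This paragraph is the article's only justification of the sample size for the primary outcome. If its figures do not fit together, a reader cannot tell what effect the trial was sized to detect or what degree of clustering it was meant to withstand. The candidate explanations describe different designs. One has ample power for 0.50 SD. Another is only just adequate for 0.50 SD under strong clustering. A third was sized for an effect of about a third of an SD.

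**Working it through.** **Inputs from the Sample size calculation section.** Effect d = 0.50; alpha = 0.05; ICC ρ = 0.01; 19 clusters; m = 20 per cluster; stated power .80.

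**Assumptions, because the article does not state them.**
- The effect size is in SD units (SD = 1).
- The test is two-sided.
- The split is 10:9. This is what balanced blocks under Randomization would give: eight paired hospitals split 4:4 and the other eleven split 6:5.

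**Step 1: the plan's own figure.**
- Design effect: DE = 1 + (m − 1)ρ = 1 + 19 × 0.01 = 1.19.
- Effective sample size: 380 / 1.19 = 319.
- Standard error: SE = √[DE × (1/200 + 1/180)] = √(1.19 × 0.010556) = 0.112 SD.
- Noncentrality: 0.50 / 0.112 = 4.46.
- Normal approximation: power = Φ(4.46 − 1.96) = Φ(2.50) = 99.4%.
- Noncentral t, 19 − 2 = 17 df, critical value 2.110: power = 98.7%.

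The stated .80 is not reproduced.

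**Step 2: do the assumptions matter?** At ICC 0.01, changing one assumption at a time (t, 17 df):

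| Variant | Power |
|---|---|
| 11:8 split | 98.6% |
| One-sided test | 99.6% |
| Unequal cluster sizes, coefficient of variation 1.0 | 97.3% |
| 15 patients per hospital | 96.1% |

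None comes near 80%.

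**Step 3: sample size for 80% power at the stated inputs.**
- m = 7: DE = 1.06, total 133, power 79.9% (normal) or 75.0% (t).
- m = 8: DE = 1.07, total 152, power 84.5% (normal) or 80.1% (t).

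So about 7 to 8 patients per hospital would suffice, against the 20 stated.

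**Step 4: what would give .80 with 19 × 20?** For 80% power, d/SE must be 1.960 + 0.842 = 2.80 (normal) or about 2.97 (t, 17 df).
- Hold d = 0.50 and solve for ρ. Normal: SE = 0.50/2.80 = 0.178, DE = 0.178²/0.010556 = 3.02, ρ = 2.02/19 = 0.106. By t: ρ = 0.088.
- Hold ρ = 0.01 and solve for d. Normal: 2.80 × 0.112 = 0.31 SD. By t: 2.97 × 0.112 = 0.33 SD.
- With a one-sided test at d = 0.50, the ICC would have to be about 0.13 (t).

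**Step 5: power for 0.50 SD at 19 × 20 over the range of ICC.**

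| ICC | Design effect | Power, t (17 df) | Power, normal |
|---|---|---|---|
| 0.01 | 1.19 | 98.7% | 99.4% |
| 0.02 | 1.38 | 97.4% | 98.6% |
| 0.05 | 1.95 | 90.7% | 93.6% |
| 0.10 | 2.90 | 76.8% | 81.5% |

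**The case against.** **Achieving .8 may mean at least .8.** Read that way, the sentence is literally true. But the section says that the sample size comes from a power analysis and that "power is set at .80 and alpha at .05". Solving for .80 at these inputs returns about 133 to 152 patients, not 380, so this reading leaves the derivation unexplained.

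**The mismatch is in the safe direction.** This stands. At the stated inputs the trial has more power than claimed. Power is still 97.4% at ICC 0.02, the top of the range cited for decisional conflict, and by t it falls below .80 only above an ICC of about 0.088. The multilevel analysis does not use the planning ICC. This is an error in the printed justification, not a threat to the analysis.

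**Stronger readings that the article does not support.**
- A reader might infer that the ICC was really 0.1 and is misprinted as 0.01. An ICC of 0.10 does give 81.5% by the normal approximation. But an effect of 0.31 to 0.33 SD at ICC 0.01 gives .80 equally well, and nothing in the article favours either.
- A reader might object to calling 0.01 conservative, since it is the midpoint of 0 to 0.02. But the same section cites a median of 0.0007, about one fourteenth of the value chosen. The choice is debatable rather than wrong, and moving to 0.02 costs only 1.3 points of power.
- A reader might argue that the high power lets a difference well below 0.50 SD reach significance (2.11 × 0.112 = 0.24 SD). That is not peculiar to this error. With exactly 80% power for 0.50 SD, the smallest significant difference would be about 0.35 SD (2.11 × 0.168, at 8 per hospital), also below 0.50.

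**Conclusion.** The point holds as an arithmetic inconsistency. At the stated inputs the design has about 99% power, not 80%, and 80% would need roughly 133 to 152 patients rather than 380. At least one of the effect size, ICC, sidedness or power printed is not what produced the 380, and nothing else in the article reconciles them.

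The result rests on reading .50 as SD units, a two-sided test and a 10:9 split. The last two hardly matter: the alternatives tried with 19 × 20 at ICC 0.01 all gave 97% or more. The SD reading is the natural one, but the source cited for the effect size was not available to confirm it.

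A reader might infer that the trial is underpowered. At its stated inputs it is not. Power drops to about 77% (t) to 82% (normal) only if an ICC near 0.1 was the real planning value, and the article does not say so.

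**What to change.** Rewrite the power statement in the Sample size calculation section so that it names the ICC, effect size (with its units) and sidedness actually used, and prints the power that follows from them.

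- If ICC 0.01 and 0.50 SD stand: state that 380 analysable patients give about 99% power for 0.50 SD, and 80% power for about 0.33 SD (t, 17 df).
- If an ICC near 0.1 was used: correct the ICC and give power of about 77% (t) to 82% (normal) for 0.50 SD, saying which method applies.
- If a smaller effect was used: state that effect.

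In each case, show power for 0.50 SD at ICC 0.01, 0.02 and 0.10 (98.7%, 97.4% and 76.8% by t with 17 df).

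The cost is one paragraph of text. Enrolment, endpoint and analysis do not change.

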### Randomization

Nineteen Dutch hospitals have been randomized to either ‘usual care’ (arm 1) or ‘usual care + DA’ (arm 2). With this so-called prerandomization, the conventional sequence of obtaining informed consent followed by randomization is reversed [29]. This prerandomization is needed because we make clinicians aware (when introducing the DA) of the principles of shared decision-making and the characteristics of the DA. This could affect the control group if they were recruited within the same hospital.

To prevent potential imbalance between the two arms that could arise from hospital characteristics (for example, hospital size and treatment profile), two strata were included in the randomization procedure. First, if cooperation between two hospital locations leads to overlap in medical staff or patients visiting both locations, there is a risk for contamination bias if these hospital locations are not in the same cluster. In our sample, four pairs of hospitals have this overlap in hospital staff or patient visits. To maintain variability in hospital characteristics within each cluster, only two pairs were allowed to enter the same cluster. The second criterion is related to hospital specific treatment variation. In The Netherlands, hospitals that perform robot-assisted radical prostatectomy indicate a significant larger proportion of their patients for surgery compared to other hospitals [4]. At the moment of randomization, three hospitals from our sample are known for having robotic surgery facilities to treat prostate cancer patients, and only two of these hospitals were allowed to join the same cluster.

Randomization was performed by a statistician not involved in the study and blind to the identity of the hospitals, using SPSS version 19.0 (Statistical Package for Social Sciences, Chicago, IL, USA). As a first step, the four paired hospitals were randomized (block size = 2). Next, the remaining 11 hospitals were also block randomized (block size = 6, with the last position unused). A set seed was chosen that fulfilled to the criteria that only two robot facilitated hospitals were allowed into the same cluster. The generated group order was then applied to a pre-existing list of participating hospitals, which was sorted in alphabetical order. As there is an uneven number of hospitals participating in this study, the largest cluster that was formed was identified as the intervention cluster.

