### Primary outcomes

Primary outcome is decisional conflict. The decisional conflict scale (DCS) [32, 33] evaluates the level of decisional conflict on five subscales; the feeling of being well-informed; the clarity of values; the feeling of support during the decision-making process; the feeling of uncertainty about best choice; and the effectiveness of the decision. The level of decisional conflict is measured at T1. The DSC is widely accepted and applied as main outcome measure in (PrCa) DA trials [24, 34–36].

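### The target of 475 allows for 20% loss, not the stated 25% (which leaves about 356, not 380), and the 25% is described in two ways that imply different numbers for the primary outcome; a minor correction

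*Protocol article*

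**What the plan says.** All of the sample size inputs stand in the Protocol article, Sample size calculation:

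- Effect size: "To be able to detect a clinically relevant minimum effect size [61] of .50".
- Error rates: "power is set at .80 and alpha at .05".
- Clustering: "ICC for the current trial is set conservative at 0.01".
- Evaluable number: "a design with 19 clusters of 20 patients (380 patients in total) achieves a power of .8".
- Loss: a 25% rate, introduced as making up for patients who do not return questionnaires. The recruitment total then follows from a 25% "attrition rate between the first and third questionnaire, the total sample size (rounded) will be set at 475 patients".
- Per site: "This results in a recruitment of 25 patients per hospital".

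The power analysis is for decisional conflict. Under Primary outcomes the article states: "The level of decisional conflict is measured at T1". Table 1 and the Statistical analysis section agree. The Recruitment section places T1 about 1 to 2 weeks after the treatment decision, and T2 and T3 at 6 and 12 months after T1.

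**The concern.** There are two separate difficulties in one short paragraph.

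First, the evaluable number, the loss rate and the recruitment total are all printed, and they do not agree. If a quarter of 475 recruits are lost, fewer than 380 remain. The usual cause is adding 25% of the evaluable number where the evaluable number should be divided by the fraction retained.

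Second, the paragraph gives one rate two meanings. General non-response can include failure to return the T1 questionnaire, which does remove a patient from the primary analysis. Loss between the first and third questionnaire happens after the primary outcome has been collected and cannot remove anyone from that analysis. The reader therefore cannot tell how many patients are planned for decisional conflict, or how many for the outcomes at T2 and T3. At stake is the accuracy of the sample size justification and the number against which achieved recruitment and follow-up will later be judged.

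**Working it through.** **Inputs.** From Sample size calculation: 19 hospitals, 20 evaluable patients each (380), 25% loss, 475 recruits (25 per hospital), d = 0.50, ICC = 0.01, alpha = 0.05, power 0.80. Two assumptions are needed. The test is taken as two-sided, which the article does not state. The split is taken as 9 and 10 hospitals; the Randomization section gives an uneven number of hospitals and says that "the largest cluster that was formed was identified as the intervention cluster".

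**Step 1: reproduce the stated total.**

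- 380 × (1 + 0.25) = 475, and 475/19 = 25 per hospital. Both match exactly.

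**Step 2: apply 25% loss to those recruited.**

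- Required: 380/(1 − 0.25) = 506.7, so 507 patients; 507/19 = 26.7 per hospital.
- Loss that 475 can absorb: 1 − 380/475 = 0.20.
- Left after 25% loss from 475: 475 × 0.75 = 356.25, about 356; 356.25/19 = 18.75 per hospital.
- Shortfall: 380 − 356 = 24 patients. In recruits, 507 − 475 = 32.

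The article marks the total as rounded, but rounding cannot turn 506.7 into 475.

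**Step 3: what each meaning of the 25% implies.**

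| Meaning of the 25% | Decisional conflict (T1) | Outcomes at T3 |
|---|---|---|
| Loss between T1 and T3 only | up to 475, less any T1 non-response (no allowance given) | about 356 |
| Wholly T1 non-response | about 356 | at most about 356 |

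A mixture of the two falls between these rows for the primary outcome.

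**Step 4: effect on power for decisional conflict.** With m patients per hospital:

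- design effect DE = 1 + (m − 1) × ICC
- SE (in SD units) = √[DE/(9m) + DE/(10m)]
- power by normal approximation = Φ(0.50/SE − 1.96), and by non-central t with 17 df (19 hospitals − 2)

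At m = 18.75 and ICC 0.01: DE = 1 + 17.75 × 0.01 = 1.1775; SE = √(1.1775/168.75 + 1.1775/187.5) = 0.115; 0.50/0.115 is about 4.34; Φ(4.34 − 1.96) = 0.991.

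| ICC | m (total) | DE | Power, normal | Power, t |
|---|---|---|---|---|
| 0.01 (planned) | 20 (380) | 1.19 | 0.994 | 0.987 |
| 0.01 | 18.75 (356) | 1.1775 | 0.991 | 0.983 |
| 0.01 | 25 (475) | 1.24 | 0.998 | 0.996 |
| 0.02 (top of the range cited for decisional conflict) | 18.75 (356) | 1.355 | 0.982 | 0.968 |
| 0.10 (assumption; top of the range the article calls common) | 20 (380) | 2.90 | 0.815 | 0.768 |
| 0.10 | 18.75 (356) | 2.775 | 0.808 | 0.760 |

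The drop from 380 to 356 costs 0.004 at the planned ICC (0.987 to 0.983) and 0.008 at ICC 0.10 (0.768 to 0.760), both by t.

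The stated power of .8 for 380 patients does not reproduce from d = 0.50 and ICC 0.01. That is a different question and adds no weight here.

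**The case against.** The strongest reply is that the two difficulties pull in opposite directions. The figure of 380 was derived for decisional conflict at T1. If the 25% is purely later loss, up to 475 patients are available for that outcome, well above 380, and the 356 concerns only T3 secondary outcomes, for which the article makes no power claim. If the 25% includes T1 non-response, the allowance does bear on the primary outcome. This stands. It rules out saying that the recruitment target fails to deliver the number needed for the primary analysis; that is only one of two possible readings.

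A second reply is that allowing for loss through T3 is no mistake in a trial with 6- and 12-month outcomes, and is cautious for an outcome collected at T1. This stands too. A reader might infer that the allowance is simply tied to the wrong measurement. The article does not support that, because the first description of the rate is broad enough to cover T1. The Recruitment section shows how T1 loss could arise: patients send in consent, then receive the T1 questionnaire, with a reminder if it is not completed. What remains is that one rate carries two descriptions that need reconciling.

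A third reply is that power is ample either way. On the stated inputs it is. That settles how serious the point is, but it does not make 475 the right total for 25% loss.

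**Conclusion.** The arithmetic error is certain: 475 recruits allow for 20% loss, and 25% loss leaves about 356, which is 24 below the planned 380. The ambiguity is also plain on the page. Depending on which description of the 25% is meant, the primary analysis set could be anywhere from about 356 to 475, and the T3 set is about 356 if loss reaches 25%.

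Severity is minor. A reader might infer that the primary analysis is underpowered or that more patients must be enrolled. The documents do not support either conclusion. At 356 patients, power on the stated d = .50 and ICC 0.01 is about 0.98, and even at an assumed ICC of 0.10 the slip moves it by less than 0.01. These figures assume a two-sided test, a 9 and 10 split of hospitals, and equal numbers per hospital.

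**What to change.** In Sample size calculation:

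1. Either state that 475 recruits allow for 20% loss, or keep 25% and state that about 356 patients (about 19 per hospital) would then be analysable, with the power for that number (about 0.98 at d = .50 and ICC 0.01).
2. Replace the single 25% with two stated allowances: T1 non-response among consenting patients, for decisional conflict; and attrition from T1 to T3, for the outcomes at T2 and T3 only. Give the expected number at each time point.

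The cost is a few sentences and a slightly less favourable stated figure. Enrolment, design and analysis do not change.
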